##### Brief Repeatable Battery of Neuropsychological Tests (BRB-N) (collected only at baseline T0)

The BRB-N are sensitive measurement tools aiding in identifying cognitive impairment in PwMS. This battery of tests includes the Selective Reminding Test, the 10/36 Spatial Recall Test, the Symbol Digit Modalities Test, the Paced Auditory Serial Addition Test, and the Word List Generation Test [40]. Cognitive status will be collected only at baseline*.*

### Statistical analysis

Data analysis will be performed by the SPSS 25.0 program. The data will be initially examined for normality violations, outliers, errors, and patterns of missing values; missing data will be replaced by multiple imputation techniques found in the SPSS. In the event of exacerbations, the analysis will be conducted with and without the individuals who had relapsed in order to identify any untoward effects on the outcomes. The data analysis itself will follow intent-to-treat principles. The effect of the intervention on the NHPT (aim 1), ARAT (aim 1), MAM-36 (aim 1), SF-36 (aim 2), and adherence and user satisfaction (aim 3) will be examined using the Condition × Time mixed model multivariate analysis of variance (MANOVA) followed by an inspection of the univariate F-ratios. Conditions will be a between-subjects factor and time and a within-subjects factor. Interactions and main effects will be further calculated using post hoc analyses with a correction of alpha. Effect sizes associated with univariate *F*-statistics will be expressed as eta-squared (*η*^2^), and effect sizes based on a difference in mean scores will be expressed as Cohen’s *d*. We will include cognitive scores (BRB-N) as covariates in all final statistical analyses.

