**Methods:**

Twenty-four PwMS will be recruited to the study which will be conducted at two established MS centers: (1) The Regional Center for Diagnosis and Treatment of Multiple Sclerosis, Binaghi Hospital, Cagliari, Italy, and (2) The Multiple Sclerosis Center, Sheba Medical Center, Tel-Hashomer, Israel. Participants will complete a total of three assessments focusing on upper limb functions. Both groups will receive 16 training sessions focusing on functional upper limb activities. The home-based telerehab VR intervention will comprise a custom-made software program running on a private computer or laptop. PwMS will perform several activities of daily living (ADL) functions associated with self-care, dressing, and meal preparation. Conventional therapy will focus on task-related upper-limb treatments while in a sitting position, indicative of the standard care in MS. Following 8 weeks of training, participants will complete a further outcome assessment. The same tests will be conducted 1 month (as a follow-up) after completion of the intervention.

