Therefore, the primary goal of the TEAMS (TElerehabilitation And Multiple Sclerosis) is to implement a single-blind, RCT designed to compare the effectiveness of an 8-week home-based telerehab VR program with conventional therapy in PwMS with manual dexterity difficulties. Secondary aims include (a) evaluating the impact of the programs on quality of life after the intervention and follow-up 1 month later and (b) evaluating the impact of the programs on adherence and satisfaction. A tertiary aim will be to generate effect sizes which can be used to power a larger clinical trial aimed at improving upper limb functional activities via telerehab in PwMS in Italy and Israel. We hypothesize that there will be no difference in outcomes between a home-based telerehab VR training program aimed at improving functional activities of the upper limbs compared with a conventional clinic-based program after the intervention and follow-up 1 month later. We also intend to corroborate a secondary hypothesis that performing the telerehab VR training will lead to better outcomes in quality of life and adherence to upper limb exercise.

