#### Safety considerations and adverse events

Adverse events occurring during and between treatments will be recorded and compared between groups (without statistical comparisons). Training and all measurements are non-invasive and place the subject at no risk other than those that normally may occur during functional upper limb activities. Nevertheless, the patient will be free to withdraw from the study at any time. The investigator has the right to withdraw a patient from the study due to any reason concerning the health or well-being of the patient, or in case of lack of cooperation. The reason for any withdrawal will be noted in the patient’s hospital file.

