##### Adherence and user satisfaction

Adherence to exercise will be evaluated at the end of the intervention phase by examining the patient’s exercise diaries. The User Satisfaction Evaluation Questionnaire (USEQ) will be used to assess the participants’ satisfaction with the training program [39]. The USEQ is a reliable questionnaire with internal consistency designed to evaluate the satisfaction of the user in virtual rehabilitation systems.

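### Multiple imputation with no outcome excepted can give an early stopper whose diary is missing the adherence of a completer

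*Protocol article*

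**What the plan says.** The Background section states a directional hypothesis that "performing the telerehab VR training will lead to better outcomes in quality of life and adherence to upper limb exercise". Under Adherence and user satisfaction, the only source and the timing are given: "Adherence to exercise will be evaluated at the end of the intervention phase by examining the patient’s exercise diaries".

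The Statistical analysis section gives one rule for incomplete data: "missing data will be replaced by multiple imputation techniques found in the SPSS". It adds that "The data analysis itself will follow intent-to-treat principles", and it names adherence among the analysed outcomes: "SF-36 (aim 2), and adherence and user satisfaction (aim 3) will be examined using" the same model as the other measures. No outcome is exempted from imputation.

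Early stopping is foreseen. Under Safety considerations and adverse events, "Nevertheless, the patient will be free to withdraw from the study at any time", and the investigator may also withdraw a patient for health reasons or for not cooperating. The denominator is stated in the abstract: "Both groups will receive 16 training sessions focusing on functional upper limb activities".

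**The concern.** Imputation is meant for a value that exists but was not observed, and it predicts that value from similar participants who were observed. Adherence after early stopping is different. Someone who stops after session 4 did 4 of 16 sessions. That number can be established, and stopping is the behaviour the outcome is supposed to capture.

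If the diary is absent and the stated rule is applied, the lowest values in an arm are replaced by values resembling those of people who stayed. The analysis then approximates a comparison among completers while being described as intent-to-treat. One programme is done at home and the other at a clinic, so unequal stopping is plausible. The arm that lost more people could then appear to have the better adherence, on an outcome for which the trial has declared an expected direction.

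**Working it through.** **Inputs from the article.** Planned sessions: 8 weeks × 2 per week = 16, which agrees with the abstract. Sample size: 2 × 12 = 24, as stated. The article gives no adherence mean, SD or drop-out rate, so there is no adherence figure to reproduce and everything below is an assumption shown over a range.

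**Step 1: inflation of one arm's mean.** Let completers average c% of sessions, and let k of 12 participants stop after s sessions and be imputed at the completer mean. The arm mean is too high by

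k × (c − 100·s/16) / 12.

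- Smallest case, c = 80 and s = 8: (80 − 50)/12 = 2.5 points per stopper.
- Largest case, c = 90 and s = 2: (90 − 12.5)/12 = 6.5 points per stopper.
- For k = 2 the range is 5.0–12.9 points; for k = 3 it is 7.5–19.4.

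**Step 2: when the comparison changes sign.** Let VR completers average V sessions and the clinic arm C, with k stoppers in the VR arm only. The difference in sessions actually done is

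(V − C) − k × (V − s)/12.

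Imputation from VR completers leaves the expected difference at V − C whatever k is. With V = 15, C = 13 and s = 4, the actual difference is 2 − 11k/12: +1.08 (k = 1), +0.17 (k = 2), −0.75 (k = 3), −1.67 (k = 4). The imputed difference stays at +2.00.

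Smallest k that makes the actual difference negative (difference in brackets):

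| V vs C | stop after 2 | stop after 4 | stop after 8 |
|---|---|---|---|
| 15 vs 14 | 1 (−0.08) | 2 (−0.83) | 2 (−0.17) |
| 15 vs 13 | 2 (−0.17) | 3 (−0.75) | 4 (−0.33) |
| 14 vs 13 | 2 (−1.00) | 2 (−0.67) | 3 (−0.50) |

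The range is therefore one to four stoppers on one side.

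**Step 3: does real imputation behave like this?** A simulation used 2,000 trials, 20 normal-regression imputations, values limited to 0–16, completers at 15 vs 13 sessions with residual SD 1.2, and VR stoppers at 4 sessions. Stoppers were imputed at about 14.7 sessions on average with arm in the imputation model and 13.6–13.8 without it. With three stoppers the actual difference averaged about −0.85 and the imputed difference +1.83 (arm in model) or +1.57 (arm not in model). These differ slightly from Step 2 because the cap at 16 pulls the VR completer mean below 15. The sign was reversed in about 2% of trials with one stopper, 47% with two, 97% with three and 100% with four.

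**Step 4: balance.** If k people stop after s sessions in both arms, the actual difference is (V − C) × (12 − k)/12, which keeps its sign. Partial balance weakens the effect. With 15 vs 13 and stopping after 4, three VR stoppers and one clinic stopper give (9×15 + 3×4)/12 − (11×13 + 4)/12 = 12.25 − 12.25 = 0.00, instead of −0.75.

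**The case against.** The strongest reply is that the key step is not in the text. The article fixes when diaries are read. It does not say that a stopper's diary is lost or discarded. A diary accumulates, so one kept for four sessions can be read at week 8 and scored 4 of 16, and the imputation rule, which applies only to missing data, is never triggered. This stands. A reader might infer that every early stopper has a missing adherence value; the documents do not support that. The point is limited to diaries not returned or treated as missing.

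A second reply is that the adherence formula and the imputation model belong in a full protocol or analysis plan. That would answer a complaint about missing detail. It does not answer this one: the article states an imputation rule without exception and places adherence in the analysis that the rule serves.

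Third, the sizes are assumed. This also stands. A reader might infer that two drop-outs are enough to reverse the result. In the 15 vs 13 scenario with stopping after 4 sessions, two leave the actual difference at +0.17 and three are needed. Nor should a false-positive rate be inferred: a simulated unadjusted comparison of means is not the planned MANOVA with BRB-N covariates and corrected post hoc tests. If the clinic arm loses more people, the same mechanism works against VR.

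Finally, the unequal loss would not be invisible. The article commits to CONSORT and to noting reasons for withdrawal. A reader could see unequal losses, but the adherence estimate itself would still be wrong.

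**Conclusion.** The concern holds in conditional form. Where an early stopper's diary is absent or treated as missing, the stated rule would impute a mainly completer-based value for an outcome that stopping itself determines. Under the assumed figures each such participant inflates the arm mean by about 2.5–6.5 percentage points. Reversing the sign also needs unbalanced stopping, with roughly one to four stoppers on one side depending on the completer gap and the time of stopping. The documents do not show that this will happen, only that nothing in the stated rule prevents it. It affects a secondary outcome of a 24-person pilot, but one with a declared direction, so it should be corrected before any data are analysed.

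**What to change.** In Adherence and user satisfaction, and again in Statistical analysis, define adherence for every randomised participant as sessions completed out of the 16 planned, with sessions after stopping counted as not done. State that adherence is excluded from multiple imputation.

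Take the count from the partial diary where there is one. Otherwise use the VR session data, which the Telerehab VR intervention section says are stored on the device and sent to the centre, or the therapist's record of the one-on-one clinic sessions. Two things need confirming: the article mentions no clinic attendance log, and its Discussion lists remote transmission as still to be implemented.

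Counting every session after withdrawal as not done is one defensible choice among several, so report withdrawals for health reasons separately or in a sensitivity analysis.

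The cost is a few sentences of wording and, if those records are kept, no new visits or instruments. Adherence values will be lower and more skewed when people stop, which may call for a rank-based or permutation comparison.

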#### Sample size

The sample size is based on Julious’s [31] recommendation that the rule of thumb for a pilot study is a sample size of 12 subjects per group. The justifications for this sample size are based on rationale relating to feasibility, mean and variance precision, regulatory considerations, and the expected change in the study’s primary outcome measure (NHPT). According to the literature, a 20% change in the NHPT demonstrates a clinically meaningful worsening in PwMS [32]. In our study, power will be set at 80% and alpha at 5%. Therefore, 24 subjects (12 in each group) will be required in order to detect differences between the two treatment groups (assuming non-inferiority with moderate correlations among covariates, *r*-squared = 0.50).

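### Multiple imputation is followed by MANOVA F-ratios and eta-squared, which basic Rubin's rules do not combine; a likelihood-based mixed model avoids the problem and gives the arm difference with an interval

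*Protocol article*

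**What the plan says.** All the relevant text is in the Statistical analysis section of the protocol article.

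- Software: "Data analysis will be performed by the SPSS 25.0 program".
- Missing values: "missing data will be replaced by multiple imputation techniques found in the SPSS".
- Analysis set: "The data analysis itself will follow intent-to-treat principles", so participants with incomplete data stay in.
- Test: a "Condition × Time mixed model multivariate analysis of variance (MANOVA) followed by an inspection of the univariate F-ratios". Post hoc comparisons with a corrected alpha follow. Effect sizes are eta-squared for the F-statistics and Cohen's d for mean differences.
- Covariates: the BRB-N cognitive scores enter all final analyses.

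The Sample size section adds that "24 subjects (12 in each group) will be required in order to detect differences between the two treatment groups", at 80% power and 5% alpha, on a non-inferiority assumption. The article gives neither an expected amount of missing data nor a way of bringing results from several completed data sets together.

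**The concern.** Multiple imputation produces several completed data sets. Its standard combining rules take one estimate and one variance from each set, average the estimates, and add the between-set variation to the variance. A multivariate test statistic, a univariate F-ratio and an eta-squared are not in that form. The plan therefore names a missing-data method whose natural output is a pooled estimate with a standard error, and then rests its conclusions on statistics of another kind.

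The easy shortcuts are to read F from one completed set or to average F over the sets. Both leave out the between-imputation variance, so imputed values count as if they had been observed. P-values are then too small, intervals too narrow, and the answer can depend on which set is read.

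Two stated aims are exposed. The Background section hypothesises no difference between programs, and the sample size assumes non-inferiority. Both call for an arm difference with a trustworthy interval. The tertiary aim is to supply effect sizes for powering a larger trial, and an eta-squared that varies between completed sets serves that badly.

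**Working it through.** **Inputs from the article.** 12 per arm; visits T0, T1 and T2; alpha 5%; Condition × Time test. The article states no error rate under imputation, so there is no figure of its own to reproduce.

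**Assumed inputs.** Correlation 0.7 between visits; five imputations (m = 5) by Bayesian regression on arm and earlier visits; dropout completely at random of 0, 10, 20 or 30% by T2, half of it before T1; no true treatment effect; no cognitive covariates. For scale, 10% of 24 is 2.4 people and 20% is 4.8.

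**Test in each completed set.** Let d be the vector of arm differences in change from T0 (to T1 and to T2) and V its estimated covariance matrix. Then T² = d′V⁻¹d and F = T² × 21/(22 × 2), on 2 and 21 degrees of freedom.

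**Valid pooling.** Let Q be the mean of d over sets, U the mean of V, and B the between-set covariance of d.

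- One contrast: total variance = U + (1 + 1/m)B, with a small-sample t reference.
- Multiparameter (D1) test, k = 2: r = (1 + 1/m) × trace(BU⁻¹)/k and D1 = Q′U⁻¹Q/[k(1 + r)]. This was scaled by 21/22 and referred to F with at most 21 denominator degrees of freedom.

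**Results.** False positives at nominal 5%, 6,000 simulated trials per column:

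| Reading | 0% | 10% | 20% | 30% |
|---|---|---|---|---|
| F from one completed set | 4.8% | 7.7% | 10.8% | 15.4% |
| Average F | 4.8% | 7.3% | 10.2% | 13.5% |
| Median p | 4.8% | 7.5% | 10.3% | 13.2% |
| Mean p | 4.8% | 6.0% | 7.3% | 8.3% |
| D1 pooled F | 4.8% | 4.8% | 5.2% | 4.9% |
| Pooled contrast, T1 − T0 | 5.1% | 4.7% | 4.8% | 4.3% |
| Pooled contrast, T2 − T0 | 4.9% | 4.9% | 4.1% | 3.5% |
| Five sets fall on both sides of 0.05 | 0% | 9% | 17% | 26% |

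The Monte Carlo standard error at 5% is √(0.05 × 0.95/6000) = 0.28 percentage points, so the inflation is not noise. The 0% column shows the test itself is sound. The three pooled rows show that valid pooling removes the inflation.

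**Sensitivity to the form of the test.** An ANCOVA-type F on T1 (1 and 21 degrees of freedom, same arm size, correlation and number of imputations) with 10% and 20% of T1 values missing gave 8.8% and 11.6% from one set and 7.7% and 10.4% from the average F. The sets disagreed in 11% and 20% of trials. Analysing the observed values alone gave 5.3% and 4.7%. Another run under the same three assumptions gave 7.6% and 11.1% from one set, 6.5% and 9.5% from the average F, and 4.4–4.7% from the observed data.

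**Combined range, one set or average F.** At 10% missing, 6.5% to 8.8%; at 20% missing, 9.5% to 11.6%.

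**The case against.** The strongest reply has four parts.

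1. Multiple imputation and MANOVA are not incompatible. Multiparameter extensions of Rubin's rules give one pooled F. With two arms, each between-arm contrast has one degree of freedom and pools by the ordinary rules. Cohen's d can be built from pooled mean differences. This stands in full. A reader might infer that no valid single test exists, and the D1 row above shows otherwise.

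2. The article does not tell the analyst to read one completed set or to average F. A reader might infer that the plan, followed as written, yields wrong p-values. The text does not support that: the inflation depends on a shortcut the article neither prescribes nor rules out. It also says an independent biostatistician will be involved in the analysis.

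3. The number of imputations and the pooling rule are details a journal article commonly leaves to the full protocol or analysis plan. This also stands: their absence alone would not be a finding. What the article does fix is the pairing itself, with F-ratios and eta-squared as the end point of an imputed analysis.

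4. A reader might add that the imputation model is overloaded for 24 people. The article does not say which variables enter that model, so this is conjecture and forms no part of the point. Nor does anything here depend on what SPSS 25.0 can or cannot pool, which the document does not show.

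**Conclusion.** The point holds as a conditional risk with an inexpensive improvement, not as a demonstrated error in the results the plan will produce. The stated outputs do not match what basic Rubin's rules combine. If F-ratios are read from one completed set or averaged, the nominal 5% becomes roughly 6.5–9% at 10% missing and 9.5–12% at 20%, and the completed sets conflict in about 10% and 20% of trials.

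These sizes rest on the assumed correlation, missing-data rates and five imputations, none of which the article gives. The effect is nil with complete data and nil under proper pooling. The change is worth making because it swaps the stated method for one that needs no combining step and directly delivers the quantity the no-difference question requires.

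**What to change.** For NHPT, and likewise for ARAT, MAM-36 and SF-36, replace imputation plus MANOVA with a likelihood-based mixed model for repeated measures:

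- outcomes: the T1 and T2 values;
- fixed terms: baseline value, arm, visit, arm-by-visit and the planned cognitive covariates;
- a small-sample degrees-of-freedom correction;
- report: the arm difference at T1 and at T2, each with its confidence interval.

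If imputation is kept, as main or sensitivity analysis, state that the arm contrasts and their standard errors will be pooled, or that a multiparameter pooled test will be used. State also that F-ratios will not be read from a single set or averaged.

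Cost: analysis wording only. The model can be fitted in the mixed-model procedure of the same software, needs no new data or participants, and makes the same missing-at-random assumption. The omnibus multivariate test is dropped. The model does not fill in a missing baseline or cognitive score, and a participant with neither T1 nor T2 contributes nothing to the estimate.

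### Intention-to-treat is the only analysis principle stated for a trial sized on non-inferiority; a comparability claim needs a stated margin and a supporting adherence-based analysis

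*Protocol article*

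**What the plan says.** Four parts of the protocol article bear on this point.

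- **Aim.** The Background states: "We hypothesize that there will be no difference in outcomes between a home-based telerehab VR training program" and a clinic-based one. The Abstract and the Discussion both draw the practical consequence that, if results are comparable, patients may pick the program that suits them.
- **Sample size.** The number is justified "assuming non-inferiority with moderate correlations among covariates" (R-squared 0.50), with 80% power and 5% alpha. No margin, standard deviation or sidedness is given. The only effect figure is that "a 20% change in the NHPT demonstrates a clinically meaningful worsening in PwMS", which is not called a margin.
- **Analysis.** "The data analysis itself will follow intent-to-treat principles". Missing data are multiply imputed, and the analysis is repeated with and without patients who relapse. No analysis set is defined by training received. The planned test is a Condition × Time MANOVA, which tests for a difference.
- **Adherence.** "Adherence to exercise will be evaluated at the end of the intervention phase by examining the patient’s exercise diaries". It is analysed as an outcome. The VR system also records hand movement during exercise and sends it to the center. The secondary hypothesis in the Background expects better adherence with VR.

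**The concern.** In a superiority trial, intention-to-treat is cautious because non-adherence dilutes the difference and makes the claim harder to reach. Where the hoped-for result is similarity, the same dilution helps the claim. Patients who do not train have no training effect in either arm, so the observed difference shrinks towards zero whether or not the home program, properly done, is inferior.

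What is at stake is the message that patients can choose either program without losing benefit. If that message rests on intention-to-treat alone, poor adherence could produce it. The Discussion also asks whether people can exercise effectively at home, and that question partly concerns training actually done.

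**Working it through.** **1. The plan's own figure.** The article states that "24 subjects (12 in each group) will be required". This cannot be reproduced, because margin, standard deviation (SD) and sidedness are missing. The number matches the cited advice that "the rule of thumb for a pilot study is a sample size of 12 subjects per group". Solving backwards with n = 12 per arm, 80% power and R² = 0.50:

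margin / SD = (z_α + z_β) × √(2/12) × √(1 − 0.50)

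- One-sided 2.5%: (1.960 + 0.842) × 0.408 × 0.707 = 0.81 SD
- One-sided 5%: (1.645 + 0.842) × 0.408 × 0.707 = 0.72 SD

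If the 20% NHPT change were the margin (an assumption), the SD would have to be 20/0.809 = 24.7% or 20/0.718 = 27.9% of the mean. The rates below are per unit of margin, so they do not depend on R².

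**2. How non-adherence moves the intention-to-treat difference.** Let the home program, fully followed, be worse by exactly the margin M. Let B_c and B_h be the benefits of conventional and home training, so that B_c − B_h = M. A share q does not train and gets no benefit.

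- Both arms: observed difference = (1 − q)M, a shift of qM towards similarity.
- Conventional arm only: M − qB_c. Since B_c = M + B_h, the shift is at least qM whenever the home program has any benefit.
- Home arm only: M + qB_h, a shift away from similarity.

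**3. False non-inferiority rate, shared non-adherence.** With M set so that 12 per arm has 80% power:

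P = Φ(q(z_α + z_β) − z_α)

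Example, q = 20%, one-sided 5%: Φ(0.20 × 2.486 − 1.645) = Φ(−1.148) = 12.6%.

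| q (assumed) | nominal 5% | nominal 2.5% |
|---|---|---|
| 0 | 5.0% | 2.5% |
| 10% | 8.1% | 4.7% |
| 20% | 12.6% | 8.1% |
| 30% | 18.4% | 13.1% |

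If only the conventional arm is non-adherent and B_c = 1.5M (assumed), q is replaced by 1.5q, and the nominal 5% becomes 10%, 18% and 30%.

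**4. The test actually planned.** Treat the contrast as a two-sided 5% two-sample t-test, with M again set for 80% power. The chance of a non-significant result at a true difference of M is:

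| q, shared (assumed) | intention-to-treat, effect (1 − q)M, 12 per arm | per-protocol, effect M, 12(1 − q) per arm |
|---|---|---|
| 0 | 20% | 20% |
| 10% | 29% | 25% |
| 20% | 39% | 30% |
| 30% | 50% | 37% |

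Under this mechanism the per-protocol set misses the difference less often than intention-to-treat, despite fewer patients. The 20% at full adherence shows that a non-significant MANOVA is not evidence of comparability even without this problem.

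**The case against.** The case against is substantial, and several parts of it stand.

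- **It is partly an omission.** The article refers to a fuller protocol, version 2.0, which may define a per-protocol set. The article never says that intention-to-treat is the only analysis. This limits confidence. However, it does describe its analysis approach, including a relapse-based alternative, and uses adherence only as an outcome.
- **Intention-to-treat is legitimate here.** It compares the programs as offered, adherence included. That stands, and is why it should remain the main analysis. A reader might infer that the choice is wrong or should be replaced; the article does not support that.
- **No non-inferiority test is planned.** Correct. The rates in step 3 describe the test that the sample-size assumption implies, not one that the article specifies. For the same reason, a demand that intervals exclude the margin cannot be met until a margin exists.
- **The mechanism is assumed.** A reader might infer that the plan as written does inflate false comparability claims. The article gives no adherence rate and nowhere suggests equal non-adherence; it expects better adherence with VR. That expectation does not remove the concern, since excess non-adherence in the conventional arm also favours similarity. Excess non-adherence at home does not.
- **A smaller set is more often non-significant.** This fails as a comparison with intention-to-treat under shared non-adherence (step 4). The loss of precision is real: with about 8 per arm, per-protocol power falls from 80% to about 61–64%.
- **The adherence data are imperfect.** Diaries and VR data are stated, but clinic attendance is not listed as collected. The Discussion admits that someone else might do the home sessions.

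**Conclusion.** The point holds in a conditional form. The trial is sized on non-inferiority and would use similarity as its practical conclusion, while the one stated analysis principle is not cautious for that purpose if patients in both arms, or mainly in the conventional arm, do not train. With shared non-adherence of 10% to 30%, a nominal one-sided 5% error becomes about 8% to 18%, and a nominal 2.5% becomes about 5% to 13%. These figures rest on three assumptions: the non-adherence rate, no benefit in those who do not train, and a margin back-solved from 12 per arm.

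The missing margin comes first. Without one, neither analysis can support comparability, and an adherence-based set alone would not cure that. It would be too strong to require both analyses to succeed before any statement is made: in a 24-patient pilot that also aims to generate effect sizes for a larger trial, that is a debatable trade-off.

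**What to change.** 1. Keep intention-to-treat as the main analysis.
2. State a non-inferiority margin for the NHPT, the time point, the sidedness and a confidence-interval rule. The MANOVA may remain, but its non-significance should not be read as comparability.
3. Pre-specify a supporting per-protocol analysis of the same NHPT contrast in participants who completed a preset share of the 16 sessions, judged from diaries and VR system data. If clinic attendance is to count, say that it will be recorded.
4. Report both analyses with their intervals. If they disagree, do not describe the programs as comparable without qualification.

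The cost is one further analysis, largely on data already planned, plus agreement on a margin; the article says that enrolment had not begun. The drawback is that the per-protocol set is small, less precise and not protected by randomization, and that it selects on adherence, which is expected to differ between arms. It should therefore be read as support and not as a replacement.
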